### **8.2.2      *Total Accrual***

The total accrual will be 30 (15 adolescents + 15 parents).

### **8.2.3      *Estimated Duration of Accrual***

The estimated accrual duration is 9 months

### **8.2.4      *Estimated Total Length of Study***

The estimated total study length is 12 months.

## **8.3      Data Analysis Plans**

### **8.3.1      *Primary Endpoint Analysis***

For project to be considered successful and feasible in a larger study, we determined the following benchmarks: a) 70% of those approached are enrolled in the study, (b) 10 out of 15 participating parent/adolescent dyads should complete the baseline and week 12 surveys, (c) 10 out of 15 parents receive at least 4 weeks of meal deliveries, and (d) in 10 out of 15 dyads, the adolescent and the parent each complete at least one interview (week 4, 8, or 12). We will estimate the retention rate and report it with a 95% confidence interval.

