## Study Synopsis

Food and nutrition insecurity are clinically relevant, actionable social drivers of health (SDOH) disparities in pediatric populations experiencing serious illnesses, for example, cancer. One approach being studied to address outcome disparities driven by food-related SDOH in the pediatric cancer context is to provide gift cards for an online grocery delivery platform. Prior research on compensatory cost coping with illness-related financial burden suggests that parents may stretch these food dollars by purchasing lower priced food with poor nutritional value. We also know that parents and siblings may cope with illness-related financial burden by going without food and other basics to conserve household assets to meet the needs of the adolescent who is ill, which heightens parent and siblings' risk for health disparities. Medically tailored meals (MTM; home-delivered meals tailored to medical needs of individuals with SDOH + barriers to preparing healthy food) that consider nutrition, illness-related alterations in taste, and parental time demands offer a Food is Medicine approach to addressing food insecurity-related outcome disparities in pediatric serious illness populations. In studies of adults with health conditions, MTM interventions were associated with better health outcomes and less health care spending. We extend the MTM concept to pediatric populations in which inequities in SDOH can affect serious illness outcomes, using pediatric cancer as proof of concept (POC). Our purpose is to determine feasibility of our methods and MTM intervention for a future efficacy trial to improve food and nutrition security for households of children at risk for poorer cancer outcomes due to inequities in food-related SDOH. We will accomplish our objective by collaborating with a small business that makes tasty, healthy frozen meals with start-up funding from National Institute of Minority Health and Health Disparities. Our primary objective is to determine feasibility of recruitment and retention for a future efficacy trial involving an intervention that provides healthy, frozen meals tailored to tastes of children in the adolescent sub-group (ages 12-17.9 years) who are undergoing chemotherapy feasible and acceptable to the adolescents and their primary parental caregiver. We will collect quantitative and qualitative data at multiple time points from adolescents undergoing chemotherapy and their parents to inform rapid, data-driven refinements in our methods and intervention. Our results will inform the potential and protocol for a future full-scale trial and cost effectiveness studies that inform policies extending healthcare financing models to include MTM in pediatric outpatient settings where children with serious illness receive care.

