| Type                        | Single-arm feasibility study                                                                                                                                                                                                                                                                                                                                                                                                                                                                                                                                                                                                                                                                                                                                     |
| Rationale:                  | Our primary research question: is an intervention that provides healthy, frozen meals tailored to tastes of children undergoing chemotherapy feasible and acceptable to the children and their primary parental caregiver?                                                                                                                                                                                                                                                                                                                                                                                                                                                                                                                                       |
| Target Population:          | Pediatric cancer patients who have received chemotherapy                                                                                                                                                                                                                                                                                                                                                                                                                                                                                                                                                                                                                                                                                                         |

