Food is Medicine interventions (conjunctions of food and healthcare that aim to increase access to nutritious food and thus support health)[44] include offering: (a) prescriptions for produce (vouchers for food items that may require preparation), (b) medically tailored groceries (food items that may require preparation), and (c) MTMs (home-delivered, ready to heat-and-eat meals designed by a registered dietician).[44] MTMs are the most intensive type of Food is Medicine intervention, indicated for persons with substantial physical and/or contextual barriers to preparing healthy meals. Contextual barriers apply to households in which parents navigate the caregiving demands of serious pediatric illness. Short term MTMs (high risk pregnancy), or long-term MTMs (AIDS, diabetes, organ failure) improve outcomes and reduce health care costs for adult populations with SDOH inequities. [25, 44] To our knowledge, MTM interventions have not been tested in pediatric serious illness populations for which nutrition is a known, important predictor of treatment success, long-term health, and well-being. Historically, needs of pediatric populations have received little attention – children lack political clout and thus disparities for pediatric populations persist.[45] This study is a first step towards system-level interventions that embed equity into holistic care delivery for pediatric populations with serious illness. Areas of uncertainty to be addressed by this feasibility study prior to deciding whether to proceed with a future definitive trial [46] include the (a) feasibility of recruiting and retaining a sample; (b) feasibility of MTM ordering and delivery, and acceptability, affordability, accessibility, and appropriateness of MTM for the target population, and (c) sensitivity of proposed pathways to MTM.

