## **2 STUDY OBJECTIVES**

### **2.1 Primary Objective**

*2.1.1 To determine feasibility of recruitment and retention for a future efficacy trial of “Medically Tailored Meals-Kids (MTM-Kids)”, a food is medicine intervention to mitigate food and nutrition insecurity for households of adolescents in active treatment with chemotherapy for pediatric cancer*

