### **2.2 Secondary**

*2.2.1 To determine participant-reported acceptability, appropriateness, feasibility, affordability, and accessibility of the MTM-Kids intervention to mitigate food insecurity for households of adolescents in active treatment for pediatric cancer.*

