### **3 STUDY ENDPOINTS**

#### **3.1 Primary Endpoint**

- 3.1.1 *Feasibility of recruitment and retention of a study sample for a future efficacy trial of MTM-Kids intervention to mitigate food-related insecurities for households of adolescents in active treatment with chemotherapy for pediatric cancer is defined as 70% enrollment, 70% completion of baseline and Week 12 surveys, and 70% receipt of at least 4 weeks of meal deliveries + completion of at least one interview by adolescent and by parent (either week 4, 8 or 12)*

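### Section 8.3.1 declares the whole project successful on recruitment and retention benchmarks alone, although the Study Summary's primary question also asks whether the meals are acceptable

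*Protocol*

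**What the plan says.** **Where acceptability is part of the primary question.** The Rationale row of the Study Summary reads: "Our primary research question: is an intervention that provides healthy, frozen meals tailored to tastes of children undergoing chemotherapy feasible and acceptable to the children". The question extends to the parental caregiver as well. In the Synopsis, the sentence that gives the primary objective begins with recruitment and retention and then runs ungrammatically into "who are undergoing chemotherapy feasible and acceptable to the adolescents and their primary parental caregiver".

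**Where recruitment and retention alone are primary.** Section 2.1 gives the primary objective as "To determine feasibility of recruitment and retention for a future efficacy trial". The primary endpoint in 3.1 "is defined as 70% enrollment, 70% completion of baseline and Week 12 surveys, and 70% receipt of at least 4 weeks of meal deliveries", plus at least one interview by each member of the dyad. It contains no rating of the meals.

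**Where acceptability is secondary.** Section 2.2 reads: "To determine participant-reported acceptability, appropriateness, feasibility, affordability, and accessibility of the MTM-Kids intervention". Section 3.2.1 sets a criterion: a domain mean of at least 3 at week 12 for 70% of adolescents (two domains) and 70% of parents (five domains). Section 8.3.2 plans only the mean, SD and score range for these measures.

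**The success rule.** Section 8.3.1 states: "For project to be considered successful and feasible in a larger study, we determined the following benchmarks". Benchmark (a) is 70% enrolment among those approached. Benchmarks (b) to (d) each need 10 of 15: dyads completing the baseline and week-12 surveys, parents receiving at least 4 weeks of deliveries, and dyads in which both members give at least one interview.

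**The decision to proceed.** Section 1.2 introduces a list with "Areas of uncertainty to be addressed by this feasibility study prior to deciding whether to proceed with a future definitive trial". Item (b) of that list includes acceptability, affordability, accessibility and appropriateness.

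**The concern.** The label primary is attached to two questions of different scope. The wider one asks about feasibility and acceptability together, so a clear failure on acceptability would answer it no. The narrower one, recruitment and retention, is what the endpoint and the benchmarks measure.

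Section 8.3.1 then draws a conclusion about the project as a whole from the narrower set. Benchmark (b) is met by a completed week-12 survey whatever the ratings in it. Benchmark (d) is met by an interview that reports dislike of the meals. The 70% criterion in 3.2.1 is tied to no decision, and 8.3.2 does not plan the proportion by which that criterion is defined.

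At stake is the headline of a study meant to inform a larger trial. It could be reported as a success while the protocol's own acceptability criterion is missed, and nothing written in advance says how the two results are to be read together.

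**Working it through.** **1. Count the criteria.** Benchmarks (a) to (d) in 8.3.1 are enrolment, survey completion, deliveries and interviews. Those that use an acceptability score: 0 of 4. Under the rule as written, low ratings cannot prevent the success conclusion.

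**2. Inputs for an illustration.** From the protocol: 15 dyads; 10 of 15 for each of (b) to (d) (8.3.1); 70% for acceptability (3.2.1). Since 0.70 × 15 = 10.5, that criterion needs 11 of 15. If only 10 people answer at week 12 and the percentage is taken among respondents, 0.70 × 10 = 7 are needed. The protocol gives no expected true rates, so I assume 85% retention and 40% to 50% acceptability.

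**3. Chance that one benchmark is met.** With X ~ Binomial(15, 0.85), P(X ≥ 10) = 0.983. If (b), (c) and (d) were independent, all three would be met with probability 0.983³ = 0.950. They are likely to be positively related, in which case the joint figure lies between 0.950 and 0.983. Benchmark (a) is left aside.

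**4. Chance that the acceptability criterion is missed** (one group, one domain):

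| Assumed true acceptability | 15 respondents, P(X ≤ 10) | 10 respondents, P(X ≤ 6) |
|---|---|---|
| 40% | 0.991 | 0.945 |
| 50% | 0.941 | 0.828 |
| 70% | 0.485 | 0.350 |

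At 85% retention the number of respondents would usually fall between these two columns.

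**5. What a hard acceptability benchmark would cost.** At a true rate of exactly 70%, 11 of 15 is missed with probability 0.485 in one group. Required of adolescents and of parents, and treating the groups as independent, it is missed with probability 1 − (1 − 0.485)² = 0.73. At a true 80% the figures are 0.16 and 1 − (1 − 0.164)² = 0.30. Such a rule would be much harder to pass, so whether to add it is a real trade-off.

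**6. Check the criterion itself.** Section 3.2.1 labels a score of 3 as agreement. Sections 7.2.1 and 7.2.2 anchor the items at 1 and 5, and on the adolescent form in Appendix II the third of five options is the neutral one. Those sections also give a domain range of 1 to 4, whereas four items scored 1 to 5, summed and divided by 4, range from 1 to 5. As written, an all-neutral respondent scores 3 and counts as finding the meals acceptable.

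**The case against.** The strongest reply is that the operative text is consistent. Sections 2.1, 3.1 and 8.3.1 all make recruitment and retention primary, the statement of the study goal in 1.2 lists them first, and acceptability is explicitly secondary with its own 70% criterion. On this view one summary row and one garbled clause are an editorial slip. This stands: a reader might infer that the protocol has no hierarchy, or that its primary question is acceptability alone, and neither is supported. The Summary asks about feasibility and acceptability together, and the hierarchy is clear from section 2 onward.

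It can also be said that 1.2 already shows that the decision to proceed was meant to draw on more than 8.3.1, and that low ratings have a planned use, because the formative dyads and repeated interviews exist to refine the meals. Not making ratings a stop rule is a legitimate choice. This also stands, and it is why a hard acceptability benchmark is not required. It does not rescue the wording of 8.3.1, which speaks of the project's success and not only of recruitment and retention.

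Finally, parents order the meals themselves, so benchmark (c) partly reflects uptake, and full retention with no one satisfied is implausible. That is fair. But 4 of 12 weeks of deliveries to households screened for material hardship is weak evidence that the adolescent finds the meals acceptable.

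**Conclusion.** The point holds as a mismatch between a conclusion and its evidence. The 8.3.1 conclusion is broader than its four benchmarks support, and it differs in scope from the primary question in the Study Summary and the Synopsis. With 85% retention and 40% to 50% acceptability, a trial that meets each retention benchmark (0.98 apiece) would very probably miss the 3.2.1 criterion: 0.99 to 0.94 with 15 respondents, 0.95 to 0.83 with 10. These rates are assumptions, chosen to show that the conflict is possible and, if meals are delivered but disliked, likely. They do not predict it; at a true acceptability of 70% the miss probability is 0.48 or 0.35.

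The mismatch does not invalidate the study or its data. It concerns what may be concluded from meeting 8.3.1, which should be settled before results are seen.

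**What to change.** 1. Reword the Rationale row of the Study Summary and the primary-objective sentence of the Synopsis to match 2.1 and 3.1.
2. In 8.3.1, limit the conclusion from meeting (a) to (d) to a statement that recruitment and retention are feasible.
3. State there that the decision to proceed to a larger trial also considers the 3.2.1 result, as 1.2 implies.
4. In 8.3.2, report the proportions that define 3.2.1, with confidence intervals, beside the means, SDs and ranges.
5. Before 3.2.1 informs any decision, reconcile its cut-off and label with the five-option form, and correct the stated domain range.

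An acceptability benchmark within 8.3.1 is optional. If the sponsor wants one, step 5 must come first and the pass probabilities above should be weighed.

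The cost is wording in five places and one more table from data already collected, with no extra participants. The downside is a narrower headline conclusion.

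### The 10-of-15 retention benchmarks in Protocol 8.3.1 equal 66.7%, below the 70% that defines the primary endpoint in 3.1.1, so exactly 10 of 15 passes one section and fails the other

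*Protocol*

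**What the plan says.** Section 3.1.1 defines the primary endpoint by percentages. Enrollment and surveys read "70% enrollment, 70% completion of baseline and Week 12 surveys". Deliveries and interviews share one percentage: "70% receipt of at least 4 weeks of meal deliveries + completion of at least one interview by adolescent and by parent".

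Section 8.3.1 gives the criteria by which the project will be judged, introduced by "For project to be considered successful and feasible in a larger study, we determined the following benchmarks". There are four:

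- Enrollment, item (a), is again set at 70%, taken over the families approached.
- Surveys, item (b), become a count: "10 out of 15 participating parent/adolescent dyads should complete the baseline and week 12 surveys".
- Meal deliveries, item (c), have the same count of 10 in 15, applied to parents whose deliveries covered four weeks or more.
- Interviews, item (d), have it once more, applied to dyads: "in 10 out of 15 dyads, the adolescent and the parent each complete at least one interview".

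Enrollment keeps its 70% in both sections. The three retention items change from a percentage to a fixed count. Sections 8.1 and 8.2 set the sample at 15 dyads. Nothing in the protocol says that 10 of 15 is meant as an approximation to 70%, or which section prevails.

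**The concern.** The primary endpoint and the rule used to judge it should be the same criterion. Here the rule is one dyad easier than the endpoint on each retention component. The study has no hypothesis test, and section 8.2.1 says that its size is not based on an effect size, so the benchmarks carry the primary conclusion. If a component ends at exactly 10 of 15, the report could call retention feasible by citing 8.3.1 or not feasible by citing 3.1.1, and the choice could be made after the result is known.

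A second difference concerns deliveries and interviews. Section 3.1.1 places them under one percentage; 8.3.1 counts them as two items, one in parents and one in dyads. The protocol does not say whether the same dyad has to satisfy both.

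**Working it through.** **Inputs.** Threshold 70% (3.1.1); benchmark count 10 and denominator 15 (8.3.1, with 15 dyads also in 8.1). The true rates below are assumptions, shown as a range because the protocol gives none.

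**Step 1: the plan's figure.** 10/15 = 0.667, which is below 0.70. In the other direction, 0.70 × 15 = 10.5, so the smallest whole count reaching 70% is 11, and 11/15 = 0.733. Ordinary rounding of 10.5 also gives 11. Ten of 15 becomes 70% only if rounded to the nearest ten percent.

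**Step 2: direction of the difference.** A component with 11 or more of 15 passes both sections, and one with 9 or fewer fails both. Only a count of exactly 10 separates them, and there 8.3.1 is always the easier section.

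**Step 3: how often this matters.** Take dyads as independent with a common true rate p. Then P(X ≥ k) is the sum over x from k to 15 of C(15,x) p^x (1−p)^(15−x), and the chance of a split verdict is P(X = 10) = 3003 p^10 (1−p)^5.

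| True rate | Pass with 10 or more | Pass with 11 or more | Exactly 10 |
|---|---|---|---|
| 50% | 15.1% | 5.9% | 9.2% |
| 60% | 40.3% | 21.7% | 18.6% |
| 70% | 72.2% | 51.5% | 20.6% |
| 80% | 93.9% | 83.6% | 10.3% |

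These are per component.

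**Step 4: deliveries and interviews.** If (c) and (d) are each met by exactly 10 of 15, the smallest possible number of dyads meeting both is 10 + 10 − 15 = 5 (33.3%), and the largest is 10 (66.7%). Five is a floor. If the two items were unrelated, the expected overlap would be 10 × 10/15 = 6.7, and the chance of an overlap of exactly 5 would be C(10,5)/C(15,10) = 252/3003 = 8.4%.

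**Step 5: what a joint rule would do.** As an illustration, assume a true rate of 80% on each item.

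| Rule for deliveries and interviews | Items independent | Items fully overlapping |
|---|---|---|
| Separate counts, 10 or more on each | 0.939² = 88.2% | 93.9% |
| Separate counts, 11 or more on each | 0.836² = 69.9% | 83.6% |
| Same dyad meets both, 11 or more | 32.2% (joint rate 0.8² = 0.64) | 83.6% |

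The effect of requiring both in one dyad runs from large to none, depending on overlap.

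**The case against.** Four points can be made on the other side.

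*This is a small feasibility study, and the benchmarks are guides.* Section 8.3.1 also plans a confidence interval for the retention rate. Section 1.2 lists recruitment and retention as one of three areas of uncertainty to settle before deciding on a definitive trial. A reader might infer that the benchmarks alone decide whether the efficacy trial goes ahead; the protocol does not say so. They do, however, define success on the primary objective, and that definition appears in two forms that disagree. This part of the concern stands.

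*The disagreement bites only at exactly 10.* True, but under the assumed rates of 60% to 80% that happens in roughly 10% to 21% of studies for each component.

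*A reader might infer that 8.3.1 has broken up a criterion that 3.1.1 requires to be met jointly in each dyad.* That is the natural reading of the plus sign under one percentage, but 3.1.1 never says that the same dyad must meet both, and items (c) and (d) can be read as spelling out the plus sign. It is an ambiguity and not a proven contradiction. If the two are meant separately, this point falls and the mismatch between 10 and 11 remains.

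*A reader might take 5 of 15 as the likely joint result.* It is only the arithmetic minimum. Withdrawal and loss to follow-up (sections 6.3 to 6.5) tend to cost a dyad both deliveries and interviews, which pushes overlap up.

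**Conclusion.** The threshold mismatch is certain and rests on the protocol's own figures: 66.7% in 8.3.1 against 70% in 3.1.1, or 10 against 11 of 15. It affects the survey, delivery and interview benchmarks; enrollment is consistent. Its practical size is the chance of a component landing on exactly 10, which is 18.6% at a true rate of 60% and 20.6% at 70%, assuming 15 dyads that are independent with a common rate. On the plus sign, the documents support only the conclusion that the wording is unclear and needs one explicit statement. They do not support a claim that the joint reading is the required one.

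**What to change.** Before data are seen, put one threshold in both 3.1.1 and 8.3.1, expressed as a percentage of enrolled dyads. Section 5.4 allows replacement, so the number enrolled may not be exactly 15, and a fixed count could drift from the percentage again. Two options are open:

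- keep at least 70% and change 8.3.1 (b), (c) and (d) to match, which is 11 of 15 if 15 dyads enroll; or
- keep 10 of 15 and restate the retention components of 3.1.1 as at least two-thirds.

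In both sections, also state whether the delivery and interview conditions must be met by the same dyad or are judged separately.

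No change to sample size, visits or intervention is needed, but the choice has consequences. A cut of 11 lowers the chance of passing one component at a true rate of 70% from 72% to 52%, so a study that truly meets the target would miss that component nearly half the time. Keeping two-thirds avoids this but openly lowers the stated standard. Requiring both conditions in the same dyad may make the rule materially harder to pass, depending on overlap, and should be adopted only if that is what the investigators intend.
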